**Methods:**

The KTx360° study is supported by a grant from the Federal Joint Committee of the Federal Republic of Germany.

The study will include 448 (39 children) incident patients of all ages with KTx after study start in May 2017 and 963 (83 children) prevalent patients with KTx between 2010 and 2016.

The collaboration between transplant centers and nephrologists in private local practices will be supported by internet-based case-files and scheduled virtual visits (patient consultation via video conferencing). At specified points of the care process patients will receive cardiovascular and adherence assessments and respective interventions. Care will be coordinated by an additional case management.

The goals of the study will be evaluated by an independent institute using claims data from the statutory health insurances and data collected from patients and their caregivers during study participation. To model longitudinal changes after transplantation and differences in changes and levels of immunosuppresive therapy after transplantation between study participants and historical data as well as data from control patients who do not participate in KTx360°, adjusted regression analyses, such as mixed models with repeated measures, will be used. Relevant confounders will be controlled in all analyses.

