## Methods/design

Inclusion criteria for this study are: KTx from 2010 to 2019 that was performed at one of the two kidney transplantation centres in the German state of Lower Saxony, study participation of the (pediatric) nephrologist responsible for the patient’s follow-up, and membership of the patient in a participating statutory health insurance. Patients of all ages can be included.

Two cohorts of patients will be included in KTx360°: incident and prevalent patients. Incident patients will have their kidney transplantation during the recruitment period of the study (2017 to 2019) at one of the two transplant centers in Lower Saxony. There are about 225 kidney transplantations per year in these centers (210 adults and 15 children/adolescents). Assuming a response rate of 80% caused by non-participation of health insurances, private practice nephrologists or patients who decline participation, we expect to include a total sample of *n* = 487 (*n* = 448 adults, *n* = 39 children/ adolescents) incident patients during the 31 months recruitment period. With a rolling recruitment process and an assumed 15% drop-out rate per year due to graft loss, death or withdrawal from the study we expect to obtain data from 286 adults and 26 children/adolescents completing 2 years post-transplant observation and of 121 adults and 12 children/adolescents with three post-transplant years. Prevalent patients who had their kidney transplantation between 2010 and 2016 will be included in the study when they attend their regular follow-up care visits at the transplant centers. Under similar conditions as the incident patients and an assumed 5% mortality rate per year for adults before study inclusion, we expect a total of *n* = 1046 prevalent patients (*n* = 83 children/adolescents) to participate in the study.

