Study patients can be compared with two different control groups based on claims data. The first control sample comprises historical data of the prevalent patients enabling comparisons between post-transplant care before and after implementation of KTx360° for patients of the two kidney transplant centres in Lower Saxony (historical comparison group). Second, all participating health insurance companies will provide claims data of their insurants who received a kidney transplantation in a non-participating German transplant centre between 2010 and 2019 (external comparison group). In Germany, there are 2074 kidney transplantations per year [5] with about 5% of transplantations in children or adolescents under the age of 20 years. Taking into account 10% of patients with private health insurances, a response rate of 70% (because not all statutory insurances are participating) and a mortality rate of 5% per year for adults, results in available data of about 12,413 patients in their first year after transplantation. Subtracting the number of study participants (*n* = 1533), we expect to receive claims data on about *n* = 11,533 patients with kidney transplantations in the external comparison group.

An a-priori power analysis for the primary outcome of a 20% reduction of health care costs due to hospitalizations (see section on endpoints below) was conducted based on data of one statutory health insurance. According to these data, average costs of hospital treatments in the first 2 years after transplantation are estimated 19,000 € per patient. The power analysis for the effect of a 20% reduction (two-sided test) was performed in SAS 9.3 under the following assumptions: pooled standard deviation of 10,000, normal distribution, and α = .05. With the expected sample size in year one and two after transplantation of *n* = 286 incident adults, a power of .995 was estimated to find the assumed difference. Thus, we expect sufficient power to detect the hypothesized effect.

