### Study endpoints

The primary endpoint of the study will be the 20% reduction in health care costs due to a reduction of hospital utilization of study participants as compared to the control groups (endpoint 3).Increase of adherence for outpatient visits. Goal: Participation in 90% of scheduled visits.Increase of adherence to immunosuppressive therapy. Goals: 1) Coefficient of variation of levels of immunosuppressants <0.4 in 75% of patients. 2) Non-adherence in BAASIS-interview <10% in incident and <20% in prevalent patients / year.Reduction of transplant-associated complications. Goals: 1) Reduction of hospitalization costs by 20% as compared to a control group (primary endpoint) 2) Reduction of graft losses by 25% as compared to a control group.Improvement of cardiovascular fitness and stabilization of weight. Goals: 1) Reduction of hospitalizations caused by cardiovascular complications by 25% as compared to a control sample. 2) Stable weight (weight ± 5%) in patients with a baseline Body Mass Index >18.5 kg/m^2^
Quality of life of the participants will significantly improve. Goals: 1) In the mental subscale of SF-12, 80% of the participants will achieve results that do not differ from norms for the general population. 2) In the physical subscale, 20% will reach results comparable to the general population.Establishment of Standard Operating Procedures (SOPs) including all sectors of the German healthcare system. Finalization of SOPs within 48 weeks of study start.Implementation of an internet-based case file including all sectors of care. Goal: 75% of patients will have used the internet-based case file after 12 months of study start.Implementation and acceptance of telemedicine visits. Goal: 80% of participating physicians will use a telemedicine visit at least once in 80% of their patients within 12 months.

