To evaluate the goals longitudinal and cross-sectional analytic procedures are used. In both, comparisons between the included patients and the control groups are conducted if applicable. Longitudinal analyses will be conducted with regression analyses in mixed models with repeated measures. This approach is feasible to estimate within-person change over time and group differences in within-person change over time. Cross-sectional group comparisons will be analyzed with regression models without repeated measures. All models will be adjusted for possible confounders, such as age of patients, distance to transplant center or co-morbidities. Descriptive statistics will be conducted to illustrate results, achievement of endpoints (see section on endpoints) and sample characteristics. All effects will be tested with a significance level of *p* = .05.

Group differences in within-person change and levels at one point in time will be evaluated with data available for the comparison groups (mainly data from statutory health insurances). For example, in year one after transplantation costs for hospitalizations of incident patients who received their transplantation in 2017 are expected to be lower as compared to the historical comparison group (prevalent patients with transplantation between 2010 and 2016) and as compared to the external control group (with transplantation in 2017 at different transplant centres). Additionally, data on adherence assessed with the BAASIS interview of prevalent patients who are included in the study 12 months after transplantation can be compared to the adherence scores of incident patients in month 12 after transplantation.

For data of the psychosomatic and cardiovascular assessments, the evaluation of process and health status are assessed in regular visits of the participating incident and prevalent patients: Within-person change after transplantation will be analyzed. For example, we would expect positive changes in quality of life in incident and prevalent patients during the study period. We would also expect an increase in usage and acceptability of telemedicine treatments among the nephrologists.

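### The historical comparison group is built only from patients who survived and still attended after May 2017, so comparing it with incident patients followed from transplantation carries survivor bias

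*Protocol article*

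**What the plan says.** Methods/design names two control groups. The first is the past claims of the enrolled prevalent patients: "The first control sample comprises historical data of the prevalent patients enabling comparisons between post-transplant care before and after implementation of KTx360". These patients, transplanted between 2010 and 2016, "will be included in the study when they attend their regular follow-up care visits at the transplant centers". Recruitment cannot precede the study start, since the Abstract defines incident patients by "KTx after study start in May 2017". When sizing the prevalent sample, the article deducts "an assumed 5% mortality rate per year for adults before study inclusion".

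The second, external group is defined differently: insurants of the participating insurers who were transplanted at other German centres in 2010 to 2019, with no condition of later attendance.

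Evaluation and study analyses gives an example of use. Year-one hospitalization costs of incident patients transplanted in 2017 are expected to be lower "as compared to the historical comparison group (prevalent patients with transplantation between 2010 and 2016"), and also lower than in the external group. Study endpoints sets a 20% reduction in hospitalization costs (primary) and "Reduction of graft losses by 25% as compared to a control group", without naming the control group. The same evaluation section calls selection bias unlikely, on the grounds of centre, nephrologist and insurer coverage.

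**The concern.** To be in the historical group a patient must be alive and still attending the centre at inclusion, which is from a few months to more than seven years after transplantation. Incident patients face no such condition: they are transplanted during recruitment, and their early deaths and graft losses can occur under observation. The year-one comparison therefore sets one group selected on its later outcome against one that is not. This is survivor (immortal-time) bias.

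Two results are exposed. The first is the primary endpoint wherever hospital costs are compared with the historical group. The second is the graft-loss goal, if it is judged against that group: the Background counts death with a functioning graft among the main reasons for graft loss, and no such death can precede inclusion.

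The coverage argument in the article does not answer this, because full coverage of centres and insurers says nothing about who is still alive to enrol. Adjustment for age, distance or co-morbidities cannot bring back patients who are absent from the data.

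**Working it through.** **Inputs from Methods/design.** "There are about 225 kidney transplantations per year in these centers (210 adults and 15 children/adolescents"), an 80% response rate, seven transplant years (2010 to 2016), and 5% adult mortality per year before inclusion. From the Background: about 8% graft loss in three years.

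**Step 1. Reproduce the plan's prevalent sample.** Adults per year: 210 × 0.80 = 168. With k yearly deductions for the cohort transplanted in year 2017 − k:

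168 × Σ 0.95^k (k = 1 to 7) = 962.9.

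The article gives 1,046 including 83 children, so 963 adults. The figure reproduces with mortality alone; nothing is deducted for graft loss.

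**Step 2. How many are removed by death.** Without the deduction: 168 × 7 = 1,176. Removed: 1,176 − 963 = 213, or 18.1%. By cohort this runs from 5.0% (2016) to 1 − 0.95^7 = 30.2% (2010).

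**Step 3. How many die inside the cost window.** Only these patients have early costs that are plausibly tied to early failure.

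- Year one: 1,176 × 0.05 = 58.8, about 59 (5.0%).
- Years one and two: the 2016 cohort has one deducted year, 168 × 0.05 = 8.4. The other six cohorts have two, 6 × 168 × (1 − 0.95²) = 98.3. Total 106.7, about 107 (9.1%).

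**Step 4. Effect on mean cost.** Let q be the share removed and k the ratio of their early cost to that of the other patients. The documents give no value for k, so a range is shown. The full mean is (1 − q + qk) times the survivors' mean, so the understatement is 1 − 1/(1 + q(k − 1)). If programme patients truly cost 80% of the full mean, the observed reduction is 1 − 0.8 × (1 + q(k − 1)).

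| k | Year one (q = 0.050): understatement | Observed reduction | Years one and two (q = 0.0907): understatement | Observed reduction |
|---|---|---|---|---|
| 0.5 | −2.6% | 22.0% | −4.8% | 23.6% |
| 1 | 0% | 20.0% | 0% | 20.0% |
| 1.5 | 2.4% | 18.0% | 4.3% | 16.4% |
| 2 | 4.8% | 16.0% | 8.3% | 12.7% |
| 3 | 9.1% | 12.0% | 15.4% | 5.5% |

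A negative understatement means that the historical mean is too high and the programme looks better than it is.

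**Step 5. Graft loss.** Suppose the true rates are 8% without the programme and 6% with it (exactly the 25% goal), and a fraction f of patients with graft loss still enter the historical group. The rate seen there is 0.08f / (1 − 0.08(1 − f)).

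| f | Historical rate seen | Ratio, programme to historical |
|---|---|---|
| 0 | 0% | none exists |
| 0.25 | 2.1% | 2.82 |
| 0.5 | 4.2% | 1.44 |
| 0.75 | 6.1% | 0.98 |
| 1 | 8.0% | 0.75 |

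The value of f is not in the documents. For losses through death it is zero by construction.

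**The case against.** The strongest reply is that the consequences are limited, and much of it stands.

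- **Graft-loss endpoint.** A reader might infer that the goal can no longer be evaluated. The documents do not support that. The goal names no particular control group, comparisons are made only where applicable, and the external group is defined by transplantation.
- **Almost no graft losses before inclusion.** This too is tempting, but only the absence of deaths follows by construction. No inclusion criterion requires a functioning graft, and the 963 contains no deduction for graft loss. The 15% yearly drop-out that includes graft loss is stated for incident patients. Under-representation of patients back on dialysis is probable, because entry runs through regular transplant follow-up, but it is not established.
- **Size.** Applying a cost multiplier to all 18% removed would give an understatement of 8%, 15% or 27% for k = 1.5, 2 or 3. That is not justified: most of the 213 died after the cost window, and a death in year six gives no reason to assume high costs in year one.
- **Direction.** Nothing in the documents shows that excluded patients cost more. Early death also shortens the time in which costs accrue.
- **Offset.** The 286 adults in the power analysis are those expected to complete two years after drop-out for graft loss, death or withdrawal. If the two-year analysis is limited to them, the incident side is survivor-selected as well.
- **Other analyses.** Within-person change is already planned, and the year-one comparison is given as an example beside the external one.

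None of this repairs the historical group itself. It remains the only same-centre control, its definition and use are stated in the article, and no correction is described.

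**Conclusion.** The point holds for between-group comparisons with the historical group. That group is selected on survival and continued attendance after May 2017, and the article's own 963 confirms that deaths are taken out.

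For costs, the distortion is about 2% to 9% of the mean in year one and 4% to 15% over two years if early deaths cost 1.5 to 3 times as much as other patients. That is not negligible against a 20% target, but it does not by itself overturn the comparison. These figures rest on the plan's constant 5% yearly mortality and on an assumed cost ratio. They count deaths only, so patients lost to follow-up for other reasons come on top. The direction is uncertain.

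For graft loss, the historical group is unsuitable as a yardstick: a programme that meets its goal could look neutral or harmful against it. The external group remains valid in this respect.

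**What to change.** Define the historical comparison group as all insurants of the participating insurers who were transplanted at the two centres in 2010 to 2016, whether or not alive and whether or not enrolled, and follow them in claims from the date of transplantation. With the article's 80% factor this would be about 1,176 adults in place of 963. The insurers already deliver claims on non-participants selected by transplantation for the external group, so the cost is a somewhat wider claims request and a change to the evaluation wording. No new patients or visits are needed.

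If that extract cannot be obtained, count prevalent patients only from inclusion (delayed entry), use their earlier history only for within-person analyses, and judge the graft-loss goal against the external group alone. This costs only wording, but it gives up the same-centre between-group comparison with care before the programme, since prevalent patients are in the programme from inclusion onward.

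In either case, the article's statement that selection bias is unlikely should be amended to address survival to inclusion.

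### The .995 power leaves out between-centre variance, although the external cost comparison sets two programme centres against other centres

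*Protocol article*

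**What the plan says.** The power paragraph under Methods/design in the protocol article rests on four statements:

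- Test and effect: "The power analysis for the effect of a 20% reduction (two-sided test) was performed in SAS 9.3 under the following assumptions".
- Control mean: "average costs of hospital treatments in the first 2 years after transplantation are estimated 19,000 € per patient".
- Variability and error rate: "pooled standard deviation of 10,000, normal distribution, and α = .05".
- Sample size and result: "286 incident adults, a power of .995 was estimated to find the assumed difference".

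Neither the size nor the identity of the control group behind this result is given.

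On the design, the same section limits the programme to patients whose transplantation was "performed at one of the two kidney transplantation centres in the German state of Lower Saxony". It then defines two comparators. The historical group allows "comparisons between post-transplant care before and after implementation of KTx360° for patients of the two kidney transplant centres in Lower Saxony". The external group consists of insured patients "who received a kidney transplantation in a non-participating German transplant centre between 2010 and 2019 (external comparison group").

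On the analysis, Evaluation and study analyses says: "Longitudinal analyses will be conducted with regression analyses in mixed models with repeated measures". The stated purpose is change within a person and group differences in that change. Cross-sectional comparisons use regression without repeated measures. Covariates are given as examples (age, distance, co-morbidities), and centre is not among them. That section also gives, as a planned example, first-year hospitalisation costs of incident patients against external patients transplanted elsewhere in the same year.

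**The concern.** In the external comparison, exposure is nested in transplant centre: every treated patient belongs to one of two centres and no control does. Hospital cost plausibly depends on local admission and coding practice, so two centres may differ from the rest by some amount without any programme. Patient-level standard errors do not contain that variation. More patients shrink the patient-level part of the variance and leave the centre-level part untouched.

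Two things are at stake. The .995 describes a simpler comparison than the external one. And a patient-level test on the primary endpoint could declare a cost reduction that is ordinary variation between centres. The article's Discussion says that positively evaluated elements can enter standard care in Germany, so a false-positive cost result would have consequences.

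**Working it through.** **Inputs from the article.** Difference 0.20 × 19,000 = 3,800 €; SD 10,000 €; two-sided α .05; 286 incident adults; 2 programme centres; about 11,533 external patients over 2010–2019.

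**Assumptions (not in the article).** Between-centre ICC of .005 to .05; 20 or 38 external centres; about 2,000 concurrent external patients as a smaller alternative to 11,533; an even split of 143 patients per programme centre where a design effect is used.

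**Step 1: reproduce the stated power.** With 286 independent patients per group:

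SE = 10,000 × √(2/286) = 836 €; 3,800/836 = 4.54; power = Φ(4.54 − 1.96) = .995.

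The noncentral t gives .9950. Reading 286 as the total (143 per group) gives .895, or .893 with t, and does not match. The published figure is therefore the independent-patient calculation with 286 per group.

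**Step 2: the floor set by two programme centres.** The centre-level variance on the programme side is SD² × ICC/2, so SE ≥ 10,000 × √(ICC/2):

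- ICC .005: 500 €
- ICC .01: 707 €
- ICC .02: 1,000 €
- ICC .05: 1,581 €

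At ICC .02 the floor alone exceeds the 836 € behind .995.

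**Step 3: external comparison with a large control group.** With K external centres and n controls:

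True variance = 10⁸ × [ICC/2 + (1 − ICC)/286 + ICC/K + (1 − ICC)/n]

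Naive variance = 10⁸ × (1/286 + 1/n)

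Type I error = 2 × P(Z > 1.96 × naive SE / true SE); power = Φ(3,800/true SE − 1.96).

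The naive SE is 632 € for n = 2,000 and 599 € for n = 11,533. Worked case, ICC .01, K = 38, n = 2,000: true SE = 960 €; 1.96 × 632/960 = 1.29, type I error .197; power = Φ(3,800/960 − 1.96) = .977.

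| ICC | K = 38, n = 2,000: type I / power | K = 20, n = 11,533: type I / power | K = 38, n = 11,533: type I / power |
|---|---|---|---|
| .005 | .127 / .997 | .140 / .998 | .136 / .998 |
| .01 | .197 / .977 | .217 / .979 | .211 / .982 |
| .02 | .303 / .885 | .330 / .884 | .322 / .894 |
| .05 | .475 / .591 | .505 / .580 | .496 / .596 |

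These powers use normal critical values. With a t reference on centre-level degrees of freedom and 11,533 controls they are slightly lower: .995–.997, .967–.976, .851–.878 and .54–.58.

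**Step 4: only 286 controls, as the stated calculation implies.** Applying the design effect 1 + 142 × ICC to both groups (so the controls also sit in centres of 143):

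| ICC | Design effect | Power |
|---|---|---|
| .005 | 1.71 | .935 |
| .01 | 2.42 | .832 |
| .02 | 3.84 | .640 |
| .05 | 8.10 | .358 |

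Power reaches .90 at ICC .0068 and .80 at ICC .0115. This is the unfavourable case: 286 controls spread over 20 centres would give .971, .926, .812 and .538.

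**The case against.** Four points can fairly be made in defence of the plan.

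- **The models may yet include centre.** The covariate list is open, the article is condensed, and a centre effect or cluster-robust error could stand in an analysis plan that is not shown. This stands: the article does not say that patients will be treated as independent, and a reader who infers that is reading silence. What remains is that the only clustering described is within a person, and that the power figure is a finished calculation with no centre term.
- **The historical comparison uses the same two centres.** Stable differences in practice largely cancel there, leaving only centre-by-period variation. This stands in full, and none of the figures in Steps 2 to 4 apply to it. The design section also names a multiple time-series design, and external claims reach back to 2010, so a before-and-after contrast against external centres is within reach.
- **The size depends on unknown inputs.** This stands. At an ICC of .001, type I error with 11,533 external patients is only about .07. With the large external group, power at ICC .005 is about .997, no worse than the published figure. A reader might infer that the trial is underpowered. The documents do not support that at ICCs up to about .01.
- **Eligibility is not by centre alone.** The nephrologist and the insurer must also take part, and patients may decline. True, but no external patient was transplanted at a programme centre, so the nesting remains.

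**Conclusion.** The point holds for the external comparison of hospitalisation costs and for the power statement. The .995 is the power of an independent-patient test with 286 per group, and it makes no allowance for comparing two centres with others. Any non-zero between-centre ICC makes patient-level standard errors too small in that contrast. On the assumed ICCs of .005, .01, .02 and .05, the type I error of a nominal 5% test is about .13–.14, .20–.22, .30–.33 and .48–.50, nearly regardless of how many external patients or centres are assumed.

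The firm harm is false positives and intervals that are too narrow. Loss of power becomes material from an ICC of about .02 with a large external group, and earlier only if the control group is as small as 286. The conclusion does not extend to the historical comparison, and it does not establish that the final models will ignore centre.

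**What to change.** - **Power statement.** Name the comparator and control size behind .995, and restate power for the external comparison over an ICC range, for example .005 to .05.
- **External cost analysis.** Use the pre-programme claims in a centre-by-period (difference-in-differences) contrast with centre effects, so that stable centre differences drop out.
- **Inference at centre level.** Take the p-value and interval from, for example, a placebo distribution that assigns the programme label to pairs of external centres. A centre random intercept alone is a weak remedy with two treated centres and does not capture centre-by-period variation.
- **Data condition.** The placebo step needs a pseudonymised transplant-centre identifier in the claims. The definition of the external group implies that the insurers can tell participating from non-participating centres. It does not guarantee that an identifier for each centre reaches the evaluator, so delivery must be confirmed.

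The cost is wider intervals, a less favourable stated power, some extra analysis work and the confirmation of the identifier. No additional patients are needed.
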